## Methods and analysis

2

### Design and randomization

2.1

This study evaluates the “Talking mental health” prevention program using cluster randomization with a pre-post follow-up measurement approach. Elementary schools are randomly assigned to either the experimental condition or the waitlist control group by the study coordinator (SP) using digital coin toss^1^. The assignment is documented in an electronic file. Neither stratification nor block randomization are applied. The participants in the experimental condition are instructed to complete a questionnaire just before the prevention program. The post-measurement takes place at least 1 week after the intervention, and the follow-up at least 6 weeks later. In comparison, all three measurements in the waitlist control group are taken at the same time intervals, but the intervention takes place only after the last measurement.

A quasi-experimental design is used for the group of college students who carry out the prevention program. We compare students from the student organization “Vitaphilie” (Medical Students’ Association of the Heidelberg University), who are trained to deliver the program, with students from other medical student organizations not trained in the program. The students assign themselves to the student organizations independently (quasi-experimental; students carrying out the training vs. students from other student organizations).

Upon request and if needed, a psychological counseling session for the parents and subsequent parent training are offered after completion of the project (parent skills training based on EFST-P; Dolhanty et al., 2022). Parents are surveyed before and after the training, and 4 months later, and compared with parents who did not receive the training (quasi-experimental allocation).

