The Anna Freud National Center’s prevention program “Talking mental health” (TMH) is one of the few such intervention programs addressing both mental health literacy and help-seeking behavior, which is also aimed at elementary school children aged 8–10 years (Sharples et al., 2017). Although the program has been widely implemented in the UK, it has not been extensively evaluated. An initial non-control group survey revealed that the training was very well received and that the children wanted to talk more about their feelings after the training (Sharples et al., 2017). The culturally adapted and tailored version for German-speaking countries, carried out by college students, will be fully evaluated as part of this research project.

Despite the positive impacts mentioned above, increasing mental health literacy does not directly reduce existing symptoms or disability (e.g., Jorm et al., 1997). Therefore, prevention programs require complimentary and targeted interventions to alleviate psychological symptoms in children and parents under stress. Parent training programs offer a cost-effective solution, as parental factors have been found to play a crucial role in the development of mental health problems in children (e.g., Yap et al., 2014). Evidence suggests that parenting skills training (Emotion focused skills training for parents; EFST-P; Dolhanty et al., 2022) leads to a reduction in both internalizing and externalizing symptoms in children (Ansar et al., 2022; Zahl-Olsen et al., 2023). In addition, immediately after the training and at follow-ups 4, 8 and 12 months later, parental self-efficacy and emotion regulation were strengthened, and psychological distress decreased in both parents and children (Ansar et al., 2024). Emotion focused skills training for parents (EFST-P) focuses on developing the following key skills: (1) validating children’s feelings, (2) increasing motivation, (3) apologizing, when necessary, and (4) setting appropriate boundaries for children (Dolhanty et al., 2022). In this study, all children receive the universal prevention program “Talking mental health” (TMH), and families with stress are also offered Emotion focused skills training for parents (EFST-P).

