### Study procedures

2.4

An overview of the respective assessments and intervention dates can be found in Table 1. Children and students are assessed three times, parents three to six times, and teachers once. The surveys for parents, children, teachers, and students each take approximately 20–30 min. The survey for the children takes place onsite at their school and is supervised by trained staff members. The children complete the questionnaires using tablets provided by the school (online version). If tablets are not available at the school, paper-and-pencil questionnaires are used instead. Surveys for parents, students, and teachers are available online, with the participants receiving a link to the online questionnaires via email.

**Table 1 tab1:** Schedule of enrollment, interventions, and assessments.

Timepoint	Enrollment	Post-allocation					
	−t_1_	t_1_	t_2_	t_3_	t_4_	t_5_	t_6_
Eligibility screen, informed consent and allocation	X				X		
Interventions							
Talking mental health (IG)		X					
Talking mental health (CG)				X			
Emotion focused skills training					—		
Assessments							
*Parents*: stigma (PMHSS), help-seeking (GHSQ & AHSQ), mental health parents (PHQ-4), mental health children (KIDSCREEN-10), mentalizing (PRFQ)^1^, parental self-efficacy (FSW)^1^		X	X	X	X	X	X
*Children*: stigma (PMHSS), mental health literacy (vignettes), mental health (KIDSCREEN-10), help-seeking (GHSQ & AHSQ), satisfaction		X	X	X			
*College Students*: stigma (PMHSS & OMS-HC), satisfaction		X	X	X			
*Teachers*: stigma (PMHSS), satisfaction				X			

IG, Intervention group; CG, Control group; PMHSS, Peer Mental Health Stigmatization Scale; PHQ-4, Patient Health Questionnaire; KIDSCREEN-10; GHSQ, General Help-Seeking Questionnaire; AHSQ, Actual Help-Seeking Questionnaire; OMS-HC, Opening Minds Stigma Scale for Health Care Providers; PRFQ, Parental Reflective Functioning Questionnaire; FSW, Parenting self-efficacy questionnaire.

1 Only at t_4_, t_5_, and t_6_.

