To implement the project in elementary schools in Heidelberg, approval was obtained from the relevant school authorities. In addition, school administrations must agree that the prevention program and surveys can be carried out. Project staff also attend parent-teacher conferences and student body meetings to provide parents, teachers and college students with detailed information about the program. The project staff presents the project and the data collection process. Approximately 1 week later, signed consent forms are collected from the schools and students. After the parents’ school evening, all parents receive the link to the first survey (t_1_). The children in the intervention group are assessed for the first time immediately prior to the intervention (t_1_), then at least 1 week later (t_2_) and again 6 weeks later (t_3_). For children in the control group, the first assessment is scheduled after the parent-teacher conference (t_1_), 1 week later (t_2_), and at least 6 weeks later (t_3_). In the control group, the final assessment takes place just before the TMH prevention program. At the same time as the child assessments, parent assessments 2 and 3 are sent by email. Following the prevention program, teachers also receive an invitation to participate in their survey.

After the third survey, parents can request feedback based on their assessment of whether their child’s mental health is below average, average or above average compared with other children of the same age. Parents can also provide their email address if they like a psychological consultation. The consultation is conducted by a psychologist (SP) and lasts 50 min. During the consultation, the current problem situation is recorded, information about appropriate help is given, and the parent training is introduced and offered. The parent training takes place afterwards. Parents are assessed again before the parent training (t_4_), after the parent training (t_5_), and again 4 months later (t_6_). To take part in t_4_ to t_6_, parents must give their informed consent online. For this part of the study, parents who indicated in the first consent form that they would like to be contacted again are contacted. Parents who take part in the parent training and those who do not, can take part in these three additional surveys.

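### As described, the parent-training comparison for Hypothesis 4a has t4 as its only pre-training point, although the same outcomes are already measured at t1 to t3 and could limit bias from need-driven sign-up

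*Protocol article*

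**What the plan says.** Protocol article, section 2.1 (Design and randomization), on the parent training: "Parents are surveyed before and after the training, and 4 months later, and compared with parents who did not receive the training"; allocation is labelled quasi-experimental. Section 2.4 (Study procedures) gives the time points: "Parents are assessed again before the parent training (t_4_), after the parent training (t_5_), and again 4 months later (t_6". Entry is by request and need: "Upon request and if needed, a psychological counseling session for the parents and subsequent parent training are offered after completion of the project". The Introduction names the target: "families with stress are also offered Emotion focused skills training for parents (EFST-P". The comparison group is parents who do not take the training; no distress criterion is stated for it.

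In Table 1 the parent row, which includes "mental health parents (PHQ-4), mental health children (KIDSCREEN-10"), is marked at t1 through t6. The footnote restricts only the mentalizing (PRFQ) and parental self-efficacy (FSW) measures: "Only at t_4_, t_5_, and t_6". Section 2.4 counts assessments as "parents three to six times", so parents at t4 to t6 come from the t1 to t3 cohort. Section 2.8 (Statistical analysis) names demographic variables as the control for baseline group differences and describes no model specific to Hypothesis 4.

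**The concern.** Hypothesis 4a predicts better mental health in trained parents and their children, and Hypotheses 4b and 4c attribute that effect to self-efficacy and mentalization. This is a causal reading of a group that enters because it feels burdened. Such parents may be at a temporary peak, or may be persistently more distressed than others.

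One pre-training score cannot distinguish these cases, and the usual analyses fail in different ones. Change from t4 counts the fall from a temporary peak as benefit. Adjustment for t4 alone under-corrects a stable difference and makes training look harmful. Demographic adjustment addresses neither. Three earlier measurements of both Hypothesis 4a outcomes would help show which case applies, but the comparison as described gives them no role.

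**Working it through.** The article gives no sample size, expected effect or power for this comparison, so there is no planned figure to reproduce. The check is a simulation with a true training effect of zero.

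**Assumptions (not from the article).** Score at wave t = L + e_t, total variance 1, higher = more distress. Var(L) = r and Var(e_t) = 1 − r, independent over waves, so the retest correlation is r = 0.6 or 0.7. Sign-up: logit(p) = −1.5 + 0.6 × s, where s is the t4 score, the t3 score, or the stable level L in SD units. About 20% sign up. 2 million parents per scenario.

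**Spurious trained-minus-untrained difference at t5, in SD (r = 0.6 / r = 0.7; negative = apparent benefit)**

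| Sign-up follows | Change from t4 | Adjusted for t4 only | Change from t1–t3 mean | Adjusted for t1–t4 |
|---|---|---|---|---|
| t4 score | −0.23 / −0.17 | 0.00 / 0.00 | 0.00 / 0.00 | 0.00 / 0.00 |
| t3 score | 0.00 / 0.00 | +0.14 / +0.12 | −0.08 / −0.06 | 0.00 / 0.00 |
| Stable level | 0.00 / 0.00 | +0.18 / +0.15 | 0.00 / 0.00 | +0.07 / +0.05 |

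**Hand check.** The groups differ by 0.57 SD on the score that drives sign-up.

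- *t4-driven.* The gap shrinks by the factor r at any other wave, so change from t4 is −(1 − r) × 0.57: −0.4 × 0.57 = −0.23; −0.3 × 0.57 = −0.17.
- *t3-driven.* The gap at t4 and at t5 is r × 0.57 = 0.34 / 0.40, so change from t4 is zero. Adjusting for t4 leaves about (1 − r) × gap: 0.4 × 0.34 = 0.14; 0.3 × 0.40 = 0.12. The t1–t3 mean contains a third of the t3 peak: −0.23/3 = −0.08; −0.17/3 = −0.06.
- *Level-driven.* The gap is √r × 0.57 = 0.44 / 0.48 at every wave. Adjusting for t4 leaves about 0.4 × 0.44 = 0.18; 0.3 × 0.48 = 0.14 (simulated 0.15, because the within-group slope is slightly below r). Adjusting for four waves leaves the share 1 − 4r/(1 + 3r): 1 − 2.4/2.8 = 0.14 and 1 − 2.8/3.1 = 0.10, hence about 0.06 and 0.05 (simulated 0.07 and 0.05).

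**Sensitivity.** A second model lets distress persist between waves. It takes reliabilities from section 2.6 (PHQ-4 0.85, KIDSCREEN-10 0.82) and assumes a state share of 20–40% of true variance, a half-life of 4 weeks, 1 or 4 weeks from t3 to t4, 10% or 25% signing up, and a correlation of sign-up with current distress of 0.4 or 0.7. Change from t4 then shows a false benefit of about 0.04–0.29 SD at t5 and 0.05–0.45 SD at t6. Adjustment for t4 only shows a false harm of about 0.07–0.29 SD. Adjustment for t1–t4 leaves about 0.02–0.09 SD. If sign-up is unrelated to distress, all are about zero.

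**The case against.** The strongest reply is that the article does not specify a Hypothesis 4 model. It lists survey times and a comparison group, names no analysis baseline and does not exclude t1 to t3; a condensed article may leave the model to a fuller document. This stands in part. A reader might infer that the sponsor has decided to discard the earlier waves, or that regression to the mean can never be separated from a training effect in this trial. The text supports neither: the scores are collected, and Table 1 is compatible with using all six waves. What remains is that the comparison the article does state runs from t4 to t6, with only demographic adjustment named.

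The second reply concerns sequence. In section 2.4 the optional feedback and the request for a consultation come after the third survey, so score-driven sign-up may follow t3. With independent transient error, change from t4 is then unbiased. This also stands. It rules out the tempting reading that a t4-based comparison must favour the training, and equally the reading that change from the t1–t3 mean is a safe replacement: in that scenario it produces a false benefit of 0.08 / 0.06 SD. It does not rescue adjustment for t4 alone, nor change from t4 if distress persists from t3 to t4.

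Third, Hypothesis 4 is a secondary, openly quasi-experimental part of the study. That limits the importance of the point but does not remove it.

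**Conclusion.** The concern holds in a limited form. The described Hypothesis 4a comparison rests on one pre-training point in a need-driven, self-selected group, while three earlier measurements of both outcomes on these parents have no stated role. With t4 alone, the spurious effect is roughly 0 to 0.2 SD in either direction, depending on the analysis and on what drives sign-up. That range rests on assumed retest correlations of 0.6–0.7 and sign-up log-odds of 0.6 per SD, and it widens if distress persists between waves. The article gives neither these quantities nor the t3-to-t4 interval. Adjusting for all four pre-training scores keeps the error between 0.00 and 0.07 SD in every scenario of the main simulation. The earlier waves therefore reduce the problem without eliminating it.

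**What to change.** State for Hypothesis 4a that:

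- the t5 and t6 comparisons of PHQ-4 and parent-rated KIDSCREEN-10 are adjusted for all pre-training scores t1 to t4, not analysed as change from the t1–t3 mean;
- the model has a term for the original TMH arm, because TMH follows t1 in intervention schools and t3 in waitlist schools, so t2 and t3 are post-TMH in one arm only;
- the trained-versus-untrained course over t1 to t4 is reported as a pre-trend check, and Hypothesis 4a is reported as descriptive if the courses differ. Parallel courses are not proof of no bias: they fit the stable-level case, where 0.05–0.07 SD remains, in the direction of apparent harm.

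The cost is analysis wording; no new data are needed. Linkage of t1–t3 to t4–t6 is implied by the assessment counts and the code list but not stated, so confirm that the separate online consent covers it. Parents with missing early waves contribute less, some self-selection bias remains, and Hypotheses 4b and 4c gain nothing because PRFQ and FSW start at t4. Section 3.1 reports that parent recruitment is ongoing with one training group completed, so the change can be specified before most of these data exist.

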### Participants and recruitment

2.2

Elementary schools in and around Heidelberg (Germany) are invited to participate in the intervention study. Staff from our institute attended the annual conference of headmasters from elementary schools in Heidelberg and the Rhine-Neckar region. In addition, the 28 elementary schools in Heidelberg received written invitations and information about the intervention. A sample size of at least 35 classes, with 15 participating children in each class, is planned. The sample consists of elementary school children in grades 3 and 4 (approximately 8–10 years old) and their parents. Approximately 35 teachers, 45 college students implementing the prevention program and a similar number of control college students are also assessed. The inclusion criterion for the study is sufficient knowledge of written and spoken German and informed consent, with parents providing consent for their children. Teachers and parents are informed about the study both in writing (information letter) and orally (at a parents’ school evening). Children with special educational needs are included in our sample if they have sufficient German language skills to read and understand the questionnaires. If needed, children will be supported in reading the questionnaires by an integration assistant, a teacher, or a member of the project staff.

A second recruitment phase takes place after the third survey. Parents who have indicated that they may be contacted again are invited to the counseling session, parent training and follow-up surveys. For this part of the study, parents provide informed consent online.

The students carrying out the TMH program are part of a student organization of the Medical Student Council of the Heidelberg University. “Vitaphilie” is a group whose aim is to raise awareness and destigmatize mental illness. The student organization consists mainly of medical students and psychology students. The project is coordinated by the Institute for Psychosocial Prevention, which is part of the Center for Psychosocial Medicine at Heidelberg University Hospital.

### Power

2.3

The sample size of the study was determined by taking into account recommendations based on model analyses, which suggested that 35 classes of 15 students were needed to measure a moderate effect in a three-level design (Kerkhoff and Nussbeck, 2019).

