### Statistical analysis

2.8

Data will be analyzed using the intention-to-treat approach. Multiple imputation will be used to impute missing values. We will analyze and report on attrition. We will check for possible correlations between our variables, primary and secondary outcomes, as well as sociodemographics, and dropout at different time points. Additionally, we will report the reasons given by parents or children for withdrawal. The main analysis is a multilevel analysis due to the nested data structure (children in school classes). Both inter- and intraindividual differences and changes are analyzed. Demographic variables will be included in the data analysis model to control for group differences at baseline. In addition, we will examine a possible mediating effect of increased mental health literacy on increased help-seeking behavior through reduced stigma using multilevel mediation analysis. In addition, we will use correlational analyses as well as chi-squared tests, *t*-tests, Mann–Whitney-U-tests and *F*-tests for group comparisons and comparisons across time points. A significance level of *α* = 0.05 will be used. To validate the newly constructed mental health literacy scale, exploratory factor analysis (EFA) will be conducted, and the comparability of the three vignettes will be checked using ANOVAs. Qualitative data will be analyzed using Mayring’s content analysis using both deductive and inductive approaches (Mayring, 2015). On the one hand, the responses will be matched (deductively) to a pre-established coding scheme to indicate the extent to which the mental health problem is understood by the participating children, and the appropriateness of the help offered by the child. The children’s responses will be grouped blindly by two independent assessors. In the case of discrepancies, the scores will be discussed. On the other hand, categories will be formed (inductively) from the answers to gain more precise insight into the content of the children’s answers.

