In our study, we primarily relied on self-reports. In this young age group, such reports may be influenced by social desirability or other response biases (Soneson et al., 2025; Wang and Zang, 2025). Mental health stigma (Kaushik et al., 2016) or concerns regarding data security (Soneson et al., 2025) may prevent children from openly reporting whether they are seeking help or have mental health difficulties. Similar issues, including stigmatization and shame, have also been described in the context of self-reported bullying assessments (Furlong et al., 2010). In accordance with the recommendations by Wang and Zang (2025), we used neutral wording and avoided leading questions. Prior to the interview, we informed the children that their answers would be treated as strictly confidential and recorded using a number–letter code instead of their names. We also reminded them that there were no right or wrong answers. We did not include social desirability detection items or validity screening items, which should be considered in future research (Cornell et al., 2012; Wang and Zang, 2025).

In addition, only schools in the Heidelberg area are included in this first evaluation study (convenience sampling method). The socioeconomic status in Heidelberg is above German average. Therefore, we consider the influence of socioeconomic status and migration background in our evaluation. It should be noted that, so far, 12 of the 28 schools contacted have expressed interest in participating in the study. Possible differences between participating and non-participating schools will be examined and reported after data collection in order to identify possible biases. When interpreting the findings, it is important to note that the results may not be representative or generalizable. This study should therefore be understood as an initial evaluation in the German-speaking context. Future research should implement the intervention in more rural areas and different countries.

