Due to the small number of recruited schools, and for reasons of model parsimony and statistical power, we have decided not to include the school as an additional level in our main model. In exploratory analyses, we will examine variance at the school level to determine whether these differences can explain treatment effects. Due to data governance regulations, specific information at the school level, such as exact distributions of migration background and socioeconomic status, is currently not available. However, publicly accessible data from the relevant local administrative districts may serve as a reference.

This study will provide valuable insights into the effectiveness of the “Talking mental health” program in increasing mental health literacy and help-seeking behavior and in decreasing stigma. In addition, analyzing satisfaction ratings and reasons for withdrawal will offer important information regarding the acceptance and future implementation of such programs.

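### The sample-size statement counts classes while schools are randomised, so the claim that this size can measure a moderate effect is not secured

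*Protocol article*

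**What the plan says.** The only justification of size is in section 2.3, which relies on a cited recommendation that "35 classes of 15 students were needed to measure a moderate effect in a three-level design". The Participants and recruitment section (2.2) plans in the same unit: "A sample size of at least 35 classes, with 15 participating children in each class, is planned". Neither section gives a number of schools.

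The Design and randomization section (2.1) names a different unit: "Elementary schools are randomly assigned to either the experimental condition or the waitlist control group". The method is a digital coin toss, and "Neither stratification nor block randomization are applied".

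The Discussion reports that "12 of the 28 schools contacted have expressed interest in participating in the study", calls the number of recruited schools small and, citing parsimony and power, states that "we have decided not to include the school as an additional level in our main model". School-level variance is left to exploratory analyses. The Statistical analysis section (2.8) describes the main model as multilevel, with children nested in classes.

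Trial status (3.1) reports 30 classes completed and 6 more planned.

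**The concern.** Classes in the same school always receive the same condition. Any difference between schools enters the treatment contrast in full, and adding classes within a school does not average it out. The precision of the contrast is therefore limited by the number of schools, and a school-level test has degrees of freedom equal to schools minus 2. Section 2.3 counts a unit that was not randomised. Its conclusion carries over to the actual design only under conditions that the article neither states nor supports.

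The practical risk concerns interpretation. If the main result is not significant, readers may take section 2.3 as assurance that a moderate effect would have been seen. Depending on how much schools differ, the trial may not have been able to see it.

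**Working it through.** **Plan's own figure.** 35 × 15 = 525 agrees with the abstract. The requirement of 35 classes cannot be rebuilt, because target power, numerical effect size and ICCs are not given. As a plausibility check, suppose classes had been randomised 17:18. The variance per class mean is ICC + (1 − ICC)/15, with 33 degrees of freedom. Power for 0.5 SD is then 99%, 95% and 81% at class ICC 0.05, 0.10 and 0.20. So 35 classes of 15 is a reasonable size for a moderate effect if the class is the randomised unit.

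**Inputs with the school as the unit.** From the article: schools are randomised, 15 children per class, 30 + 6 = 36 classes, alpha 0.05. Assumed: 12 schools split 6:6, hence 36/12 = 3 classes each; two-sided test; moderate = 0.5 SD; 80% power for detectable effects; class ICC 0.05; school ICC 0.02 to 0.10; no dropout.

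**Formulas** (total variance 1):
- Variance per school mean: V = ICC_school + ICC_class/3 + (1 − ICC_school − ICC_class)/45
- Standard error: SE = √[V × (1/6 + 1/6)]
- Power from the noncentral t distribution, df = 12 − 2 = 10, noncentrality 0.5/SE

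Example at school ICC 0.05: V = 0.05 + 0.05/3 + 0.90/45 = 0.0867; SE = √(0.0867/3) = 0.170; noncentrality 0.5/0.170 = 2.94; power 76%.

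For the adjusted rows, V is multiplied by 0.75, on the assumption that baseline and covariates explain 25% of the variance at each level. For the class-count rows, the same total clustering is placed at class level, with 18:18 classes and df 34.

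| School ICC | 0.02 | 0.05 | 0.10 |
|---|---|---|---|
| Power for 0.5 SD, schools, unadjusted | 90% | 76% | 57% |
| Power for 0.5 SD, schools, 25% explained | 96% | 86% | 69% |
| Power for 0.5 SD, counting classes | 98% | 95% | 89% |
| Detectable effect (SD), schools, unadjusted | 0.43 | 0.53 | 0.66 |
| Detectable effect (SD), schools, 25% explained | 0.37 | 0.46 | 0.57 |
| Detectable effect (SD), counting classes | 0.35 | 0.39 (0.385) | 0.44 |

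**Break-even.** With class ICC 0.05, 80% power for 0.5 SD is kept up to a school ICC of about 0.04 unadjusted and about 0.07 with 25% explained.

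**Number of schools.** With 36 classes spread over a balanced set of schools, school ICC 0.05 and no adjustment, power for 0.5 SD is 58% with 8 schools, 76% with 12, 80% with 14 and 84% with 16.

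**Split.** Twelve unrestricted fair tosses give 8:4 or worse with probability 2 × (1 + 12 + 66 + 220 + 495)/4096 = 0.39. At exactly 8:4 the unadjusted detectable effects rise to 0.46, 0.56 and 0.70 SD.

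**The case against.** The strongest reply is that the shortfall is computed rather than documented. Every driver of the illustration except class size, class total and alpha is assumed. The trial measures before and after the intervention and puts demographic variables in the model, so an unadjusted calculation is probably too pessimistic. Dropout, also not modelled, works the other way. Twelve is the number of schools interested so far, and recruitment also ran through a regional headmasters' conference. The article admits that schools are few, presents the study as an initial evaluation, and may leave power inputs to a fuller document.

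Much of this stands. A reader might infer that the trial is underpowered, that exactly 12 schools were randomised, or that the claim holds only if schools hardly differ. The documents support none of these. At school ICC 0.02 the claim survives even unadjusted; modest adjustment moves the break-even from about 0.04 to about 0.07; and the number randomised is not stated.

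The conflict of units also stands. It concerns what sections 2.1 and 2.3 state, not an input left out, so a fuller document giving ICCs would not remove it. The admission in the Discussion explains the choice of model but does not correct section 2.3. The levels of the three-level design are not named. Occasions, children and classes is the likely reading, given section 2.8 and the Discussion. If school were meant as the third level, the number of schools would still be unstated, and the main model described in the Discussion would not match.

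**Conclusion.** The point holds in a limited form. The statement about a moderate effect rests on a unit other than the one randomised, and so it is not secured. It may still be true. Under the assumed 12 balanced schools and class ICC 0.05, power for 0.5 SD lies between 57% and 90% unadjusted, and between 69% and 96% with 25% of variance explained, over school ICC 0.02 to 0.10. Counting classes would show 89% to 98% over the same range. The pattern does not depend on the figure of 12. The size of any shortfall does depend on the realised number and split of schools, both ICCs and the gain from adjustment, none of which the article gives. The correction is worth making because it is cheap and bears directly on how a non-significant result would be read.

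**What to change.** Do not enrol more. Restate section 2.3 with the school as the unit: schools per arm as realised, classes per school, children per class, and degrees of freedom equal to schools minus 2. In place of the claim that 35 classes of 15 suffice, give the detectable effect over a stated range of school and class ICCs, with and without baseline adjustment. State that non-significant results will be interpreted against that figure and the confidence interval.

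The cost is a short calculation and a paragraph of text. The stated detectable effect will look less favourable than the present wording suggests.
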